### Adverse events

This trial includes only critically ill patients, with an inherent high risk of death and other abnormal findings associated with the underlying illness severity. We will not consider these findings as adverse events unless the investigator suspects or confirms that these events are related to the study interventions.^(
34
)^ All participating centers were trained and encouraged to report all adverse events that were judged to be potentially causally related to the study intervention.

### Sample size

Initially, the study was expected to include between 30 and 50 ICUs of the IMPACTO-MR platform, with an expected sample size of 30,000 patients (
Figure 1S - Supplementary Material
). However, owing to feasibility issues and restrictions on the study’s budget provided by the Brazilian Ministry of Health after December 31, 2023, the sample size was recalculated considering possible variations in the number of clusters, cluster size, and data from the IMPACTO-MR database to estimate the baseline rate of HCAIs. Therefore, by including 12,600 patients (21 clusters with a mean of 600 patients each) with a baseline rate of 6 HCAIs per 1,000 patient-days and a between-cluster variance of 0.6, our study will be able to detect a 9% (relative risk of 0.91) reduction in the incidence of HCAIs, with 80% power and an alpha of 5% (
Figure 2S - Supplementary Material
). Details are provided in the
Supplementary Material
.

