### Design

The CLEAN-IT trial is an investigator-initiated, multicenter, open-label, cluster-randomized crossover clinical trial assessing the effectiveness of daily chlorhexidine baths in reducing the incidence of device-associated HCAIs in critically ill patients compared with soap and water baths.

The study was conducted in 23 Brazilian intensive care units (ICUs) and is nested in the IMPACTO-MR platform,^(
29
)^ a research platform that collects prospective observational data from more than 50 Brazilian ICUs.

Each participating ICU is a cluster that was randomized to perform the interventions (CHG bathing or soap and water bathing) with crossover for a period of 3 to 6 months, depending on the time of each center’s entrance to the study, with a 1-month washout period between CHG bathing and soap and water bathing transitions.
Figure 1
shows all possible allocation sequences for the participating ICUs.

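### The stated 80% power for a 9% reduction does not fit 12,600 patients at 6 HCAIs per 1,000 patient-days: it would need a mean of about 49 ICU days per patient

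*Protocol article*

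**What the plan says.** The Sample size section explains that the original plan of 30,000 patients was cut for feasibility and budget reasons and that the size was then recalculated. The new calculation is described as "by including 12,600 patients (21 clusters with a mean of 600 patients each) with a baseline rate of 6 HCAIs per 1,000 patient-days", together with "a between-cluster variance of 0.6". From these inputs it concludes that "our study will be able to detect a 9% (relative risk of 0.91) reduction in the incidence of HCAIs, with 80% power", with alpha set at 5%. Details are referred to the Supplementary Material, which is not at hand.

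The Statistical analysis section fixes the test: two-sided at 0.05, from a Poisson mixed model for HCAIs per 1,000 patient-days with center as a random effect. The Design section describes a cluster crossover, "with crossover for a period of 3 to 6 months", with a one-month washout. The article gives no mean ICU stay, so the step from patients to patient-days cannot be read from it.

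**The concern.** The precision of a rate ratio is limited by the number of events. A crossover can remove stable differences between ICUs, but it cannot remove the counting error in the events themselves. At 6 per 1,000 patient-days, 12,600 ICU patients yield some hundreds of HCAIs for stays of ordinary length, whereas a 9% relative difference calls for thousands.

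This sentence is the article's justification for going from 30,000 to 12,600 patients. It tells the reader that the smaller trial keeps good power for a small effect. If that is not so, the 9% target is the wrong yardstick for the result.

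**Working it through.** **Inputs.** From Sample size: 12,600 patients (21 × 600), control rate 0.006 per patient-day, relative risk (RR) 0.91, power 80%, alpha 5%. From Statistical analysis: two-sided test. Assumed: equal patient-time in the two arms (6,300 patients each), and the mean ICU stay *L*, which is not given and is therefore varied.

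**Best case for the design.** Between-cluster variance cancels fully; there is no cluster-period variance, no overdispersion, and no cost for the period and interaction terms. Then SE(log RR) = √(1/E₀ + 1/E₁), where E₀ and E₁ = 0.91 E₀ are the expected events under soap and water and under chlorhexidine.

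**Step 1: events needed for the plan's own claim.**

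E₀ = (1.96 + 0.8416)² × (1 + 1/0.91) / (ln 0.91)² ≈ 1,852

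E₁ = 0.91 × 1,852 ≈ 1,685, so the total is about 3,540. The Schoenfeld and Freedman event formulas give 3,530 and 3,535.

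**Step 2: patient-days needed.** 1,852 / 0.006 ≈ 308,700 per arm, about 617,000 in all. Divided by 12,600, this is 49.0 ICU days per patient. As an illustration of scale, 617,000 / 21 is about 29,400 patient-days per ICU. If every ICU ran exactly two 6-month periods, that is about 81 beds occupied every day (29,400 / 365).

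**Step 3: power at RR 0.91 for an assumed stay.** E₀ = 6,300 × L × 0.006; power = Φ(|ln 0.91| / SE − 1.96). For L = 7: E₀ = 264.6, E₁ = 240.8, SE = 0.0891, power = Φ(0.0943/0.0891 − 1.96) = Φ(−0.90) ≈ 18%.

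| Assumed mean stay (days) | Expected HCAIs, both arms, at RR 0.91 | Best-case power at RR 0.91 | Smallest RR detectable with 80% power |
|---|---|---|---|
| 3 | 217 | 10% | not computed |
| 5 | 361 | 14% | 0.73 |
| 7 | 505 | 18% | 0.77 |
| 10 | 722 | 24% | 0.81 |
| 14 | 1,011 | 32% | 0.83 |
| 49 | 3,538 | 80% | 0.91 |

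A simulation of 21 clusters with a mean rate of 6 per 1,000 patient-days (20,000 runs) agreed: about 14%, 18–19% and 24% at 5, 7 and 10 days.

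**Step 4: can another reading reproduce 80%?** Each change below is made on its own.

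| Reading | Power at 5–10 days | Mean stay needed for 80% |
|---|---|---|
| One-sided 5% test | 23–35% | about 39 days |
| 600 per cluster per arm (25,200 patients) | 24–43% | about 24.5 days |
| 23 centers × 600 (13,800 patients) | 15–26% | 44.7 days (617,000 / 13,800) |
| Original 30,000 patients | 28–50% | 20.6 days (617,000 / 30,000) |
| 0.6 as log-rate variance around a median of 6 (mean rate 6 × e^0.3 ≈ 8.1) | 18–31% | about 36 days (49.0 × 6 / 8.1) |

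Reading 6 as 6% of patients infected gives 26%. Using 0.6 as a variance on the rate scale in cluster-trial formulas gives 12–29%. No reading reproduces the stated 80% at stays of 5 to 10 days.

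**The case against.** The strongest reply is that the Supplementary Material holds the details, including perhaps the mean stay and the scale of the 0.6 variance, and that a condensed article cannot be faulted for leaving them there. That is right as far as it goes: their absence from the article is not the point here. But the sample size, the rate, the effect and the power are printed together, and a supplement could only show how the 80% arose. It could not make those four figures agree at a plausible stay.

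A second reply is that every power figure above depends on a stay that the article does not state. This also stands. A reader might infer that the trial's real power simply is 14–24%, or that the claim is impossible in a strict mathematical sense. The documents support neither. The range belongs to an assumed stay of 5 to 10 days; at 3 to 14 days it is about 10–32%, and the log-normal reading of the variance reaches about 41% at 14 days. What holds is that the claim needs about 49 days per patient.

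A reader might also want one realistic detectable effect that includes variation between periods within an ICU. The article gives no such variance: the 0.6 is between clusters, which a crossover largely removes. The direction is certain, the amount is not.

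Finally, it is tempting to say that a null result will be reported as ruling out a modest benefit. Nothing in the article says how a null result will be read. Inclusion ended on December 31, 2023, and the power statement does not enter the analysis, so the matter is one of interpretation and does not affect the validity of the estimate.

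**Conclusion.** The point holds. The Sample size section attributes to the design a power that its own inputs do not give. Under assumptions that all favor the trial, 80% power at RR 0.91 needs about 3,540 HCAIs, and hence a mean of about 49 ICU days per patient, or about 24.5 on the most generous reading of the cluster size. Neither is plausible as a mean ICU stay.

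At an assumed mean stay of 5 to 10 days, the trial has at best about 14–24% power for a 9% reduction, and 80% power only for reductions of about 19–27%. These are upper limits on performance: cluster-period variation, overdispersion and the model's period and interaction terms can only make them worse. The source of the error cannot be identified from the article.

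**What to change.** Withdraw the 9%/80% statement. In its place give either the RR detectable with 80% power or the power at RR 0.91, computed from expected events: 12,600 × mean ICU stay × 0.006 at the baseline rate, with the chlorhexidine arm scaled by the RR. The mean stay can come from the platform database, which routinely records ICU length of stay. Add an allowance for cluster-period variance, name its source or label it as an assumption with a range, and say on which scale the 0.6 is expressed. If the supplement already holds these inputs, use them and correct its result to match. State that a non-significant result will be read by its confidence interval and not against the 9% target.

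The cost is a change of text. No extra patients are needed and the analysis is untouched. The downside is a less favorable stated figure.

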### Statistical analysis

The main analysis will follow the intention-to-treat framework with patient-level data. Each patient will be analyzed according to the group (CHG or soap and water bath) assigned to the ICU at admission, irrespective of the length of stay and the number of days the patient received each intervention. Patients whose stay crosses into another treatment period will be analyzed according to their initial assignment, and patients admitted during the washout period will not be included in the intention-to-treat analysis. We will perform a sensitivity analysis including only patients admitted and discharged during the same intervention period.

The primary outcome of HCAI incidence per 1,000 patient-days will be analyzed using a Poisson generalized mixed linear model with allocation group, study period, and the interaction of allocation group and study period as fixed effects and center as a random effect. Other possible distributions and models might be considered according to the variable’s behavior. We will use the same model to evaluate the incidence per 1000 patient-days of each specific HCAI (CLABSI, VAP, and CAUTI), rates of positive microbiological cultures for multidrug-resistant pathogens, and antibiotic use. Mortality will be assessed using survival and logistic regression models, taking the center, allocation group, and study period as random effects and the interaction of the allocation group and study period as a fixed effect. Generalized mixed linear models with appropriate distributions will be utilized for other outcomes. Preplanned subgroup analyses will be conducted according to the following characteristics: surgical
*versus*
nonsurgical admission, SAPS 3 score ≤ 40
*versus*
> 40, public
*versus*
private ICU, and ICU length of stay ≤ 7
*versus*
> 7 days.

No adjustments for multiplicity will be performed, and a 2-sided p value of less than 0.05 will be considered statistically significant. All the statistical analyses will be performed using R software (R Foundation for Statistical Computing, Vienna, Austria; https://www.R-project.org/).^(
30
)^

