## INTRODUCTION

Health care-associated infections (HCAIs) are common preventable illnesses in hospitalized critically ill patients^(
1
)^ and are associated with increased health care costs, length of stay, and mortality.^(
2
-
5
)^ Critically ill patients are at increased risk for HCAIs due to a myriad of factors, such as the use of invasive devices (endotracheal tubes, central lines, and urinary catheters) and their underlying critical illness. Practices such as care, device insertion bundles, and hand hygiene are the cornerstones of infection prevention^(
6
-
9
)^ and a major focus of infection and prevention control services, with several clinical trials evaluating infection prevention strategies in the critical care setting.^(
10
-
15
)^

Chlorhexidine digluconate (CHG) is a water-soluble, low-foaming, topical antiseptic agent included on the list of essential medicines of the World Health Organization;^(
16
)^ CHG exhibits activity against gram-positive and gram-negative bacteria, yeasts, and lipophilic viruses with a possible benefit of residual antibacterial activity.^(
17
)^ Chlorhexidine digluconate has been used in impregnated vascular catheter dressings, skin preparation for invasive procedures, preoperative bathing, and oral decontamination.^(
18
-
20
)^

The use of daily bathing with CHG to reduce HCAIs in critically ill patients has been evaluated in several studies, with mixed results indicating that it decreases the risk of some infections (central line-associated bloodstream infection [CLABSI] and bacteremia) while increasing the risk of others (ventilator-associated pneumonia [VAP]).^(
14
,
15
,
21
,
22
)^ The role of CHG bathing in reducing HCAIs has not been properly evaluated in low- and middle-income countries (LMICs), where the incidence and burden of HCAIs are greater.^(
1
,
23
,
24
)^ A cluster randomized design is desirable when studying interventions to reduce HCAIs given the possible benefit of the spillover effect and the reduction of contamination between the treatment and control groups.^(
25
,
26
)^

The Daily Chlorhexidine Bath for Health Care Associated Infection Prevention (CLEAN-IT) trial is a cluster randomized crossover trial to evaluate the use of daily chlorhexidine bathing in critically ill patients in reducing device-associated HCAIs (CLABSI, catheter-associated urinary tract infection [CAUTI], and VAP) compared with soap and water bathing.

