### Washout period

The washout period was defined as 1 month between distinct intervention periods (CHG bath period and soap and water bath period). During this period, all centers used soap and water for bathing.

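### The sensitivity set is selected on discharge date, which HCAI itself delays, so it discards infections out of proportion to patients

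*Protocol article*

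**What the plan says.** The Statistical analysis section of the protocol article sets the main analysis as intention to treat by the ICU's assignment at admission, "irrespective of the length of stay and the number of days the patient received each intervention". It adds that "Patients whose stay crosses into another treatment period will be analyzed according to their initial assignment" and that "patients admitted during the washout period will not be included in the intention-to-treat analysis". It then names one sensitivity analysis: "We will perform a sensitivity analysis including only patients admitted and discharged during the same intervention period".

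Three other places bear on this.

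- Design: each ICU is randomised "with crossover for a period of 3 to 6 months, depending on the time of each center’s entrance to the study".
- Washout period: the month between interventions is not a third exposure, because "During this period, all centers used soap and water for bathing".
- Introduction: HCAIs "are associated with increased health care costs, length of stay, and mortality".

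Study outcomes ties the primary outcome to infections that arise in the ICU and inside each intervention period.

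**The concern.** The purpose is sound: see whether the result holds in patients whose bathing did not change. But the rule uses the discharge date, which is observed after allocation and which an HCAI delays.

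Take two patients admitted 20 days before a period ends. One stays 5 days and is kept. The other develops VAP in the first week, stays 25 days and is removed, along with an infection that arose entirely under the assigned bath. Removal is thus tied to the outcome.

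The rule also matches exposure poorly. A patient from a soap-and-water period who runs into the washout stays on soap and water, yet is dropped just like a chlorhexidine patient whose bathing really changes.

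At stake is how the check is read. If its result differs from the primary one, the reader must separate three explanations: removal of crossing exposure, selection of a shorter-stay population, and loss of events.

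**Working it through.** **Plan's own figure.** There is none to reproduce. The article gives no ICU stay, no share of stays that cross a period end and no share of HCAIs among them. Stay is therefore an assumption throughout.

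**Inputs.** From the article: periods of 3 to 6 months (taken as T = 90 and 180 days), 6 HCAIs per 1,000 patient-days, 12,600 patients. Assumed: admissions uniform over the period; log-normal stay with median 4 and mean 7.5 days; an HCAI adds 5 to 15 days on average.

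**Step 1: chance of removal.** A stay of L days is removed with probability min(1, L/T). For T = 90, a 15-day stay goes with probability 15/90 = 16.7%. If an HCAI adds 10 days this becomes 25/90 = 27.8%.

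**Step 2: all patients.** The mean share is about mean stay/T: 7.5/90 = 8.3% and 7.5/180 = 4.2%, slightly more once HCAI prolongs some stays.

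**Step 3: patients with HCAI.** If risk is proportional to stay, their mean stay before prolongation is mean × (1 + CV²). For a log-normal, 1 + CV² = (mean/median)² = (7.5/4)² = 3.52, giving 7.5 × 3.52 = 26.4 days. Adding 5 to 15 days gives 31.4 to 41.4 days. Dividing by T gives 35-46% (T = 90) and 17-23% (T = 180). These are upper limits, because removal is capped at 1 and risk does not rise linearly over very long stays.

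**Step 4: simulation under the same assumptions, constant hazard from admission.**

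| | T = 90 | T = 180 |
|---|---|---|
| Patients removed | 8-9% | 4-5% |
| HCAIs removed, whole stay | 29-39% | 15-21% |
| HCAIs arising inside the period, removed | 20-31% | 10-16% |
| HCAIs kept if censored at period end | 88% | 94% |

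With no HCAI risk in the first 2 days, the whole-stay losses are 33-43% and 17-23%, the in-period losses 21-33% and 11-17%, and censoring keeps about 85-93%.

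**Step 5: other stays.** Mean 5, 7 or 10 days, CV 1, 1.5 or 2, no risk in the first 2 days and no prolongation: 2.8-11.1% of patients are removed, 7-43% of HCAIs over the whole stay, and 3-23% of in-period HCAIs.

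**Step 6: rate and rate ratio, equal periods.** Mean 7 days, CV 1.5, HCAI adding 10 days, T = 90: the control rate falls from 5.35 to 4.84 per 1,000 patient-days (0.51/5.35 = 9.5%), and the rate ratio goes from 0.917 to 0.914. For T = 180 the rate falls from 5.33 to 5.12 (3.9%) and the ratio stays at 0.919. If HCAI does not prolong stay, the rate rises slightly at T = 90 (5.63 to 5.75), so the fall comes from selection on the outcome. The largest shift in the ratio in these runs was 0.731 to 0.716, or 0.015.

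**Step 7: precision.** At a mean of 7.5 days, 12,600 × 7.5 × 0.006 = 567 HCAIs, before any effect. A loss of 29-39% is about 164 to 221 of them. With the standard error of the log rate ratio roughly proportional to 1/√events (between-centre variation ignored), it grows by a factor of 1/√0.71 = 1.19 to 1/√0.61 = 1.28. Censoring at T = 90 gives 1/√0.88 = 1.07. At T = 180 the factors are 1.08 to 1.13 under the rule and 1.03 under censoring.

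**The case against.** A reader might infer that this analysis cannot check the primary result at all. The figures do not support that. The rule is the same in both arms, the target is a ratio, and with equal periods the ratio moves by about 0.01. A clearly larger change would still say something about crossing stays.

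A reader might also infer a bias as large as the 9% target effect. With no true effect, a 90-day period in one arm and a 180-day period in the other does give a ratio of about 0.91 to 0.945, depending on the stay and hazard assumptions. But nothing in the article says that an ICU's two periods differ: "with crossover for a period of 3 to 6 months" is tied to when a centre joined. Even if they differed, the short period would have to fall in the same arm across ICUs, and sequence is randomised. Over 23 ICUs with 11 or 12 starting on chlorhexidine the simulated null ratio is 0.998 to 1.002, and with a period term it is 1.00.

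Three further limits stand. The rule does not remove long-stay patients as such: 42-78% of stays over 30 days remain under the assumptions of step 5. Part of the HCAI loss is of infections arising after period end, which the analysis is right to leave out; the in-period row of the table is the fair measure of waste. And this is the only sensitivity analysis named in the article, but the analysis plan and supplement are not shown, so the absence of others is no finding.

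The strongest reply is textual. If Study outcomes means that only in-period infections count, the primary analysis is already censored and the proposed replacement would largely repeat it. That stands as a reason to settle the reading, not as a defence of selecting on discharge date.

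**Conclusion.** The point holds in limited form. The stated rule selects on a post-allocation quantity that the outcome prolongs, and it removes HCAIs at several times the rate at which it removes patients, including infections with clean exposure. Under the assumed skewed stays, the waste of in-period HCAIs is about a fifth to just under a third with 3-month periods and about 10-16% with 6-month periods. It could be as low as 3% with short, less skewed stays and no prolongation.

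The consequence is lost precision, a lower rate in a selected shorter-stay population and a less interpretable check. It is not a large bias in the rate ratio when periods are equal. The simulations did not cover bathing that itself changes length of stay or mortality, where selection could matter more. The intention-to-treat analysis keeps every patient admitted in an intervention period and is unaffected.

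**What to change.** Replace the sentence with a rule that does not use the discharge date: include every patient admitted in an intervention period, and count HCAIs and patient-days only up to the earlier of ICU discharge and the last day of that period. Keep the admitted-and-discharged set at most as a supplement.

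At the same time, state whether the primary analysis counts HCAIs after period end. Study outcomes can be read as stopping at the period boundary, while Statistical analysis can be read as following the whole stay under the initial assignment. The censored analysis is distinct only under the second reading.

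The cost is a sentence or two of wording. It needs only the admission, discharge, infection and period dates that the planned analyses already require. The downside is that patient-days after period end go unused in this sensitivity analysis.

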## DISCUSSION

The CLEAN-IT trial is the first multicenter, randomized clinical trial evaluating the effect of daily bathing with CHG to reduce HCAIs in critically ill patients in an LMIC; it is also expected to be the largest trial in the literature on the subject.

When designing the CLEAN-IT trial, the steering committee faced important issues that should be discussed. One of the distinct aspects of the study is that we chose to use a 2% CHG solution instead of CHG-impregnated bathing cloths. In Brazil and other LMICs, the financial costs of CHG-impregnated bathing cloths would jeopardize the implementation of the intervention if it proves to be effective on a large scale. Therefore, our aim with this protocol was to evaluate a cheaper and readily available intervention with high external validity.

Additionally, we chose to use patient-days as the denominator for the reporting of HCAI incidence instead of device-days given the simplicity and accuracy of patient-day data collection and the equivalence of both metrics and their use in similar studies.^(
1
,
22
,
35
)^

Another design issue is the rationale for performing a cluster randomized trial instead of an individual randomized trial. Bathing practices in intensive care units are usually interventions decided at the unit level and not at the individual level, allowing more uniform delivery of the intervention, due to both the type of intervention and logistical convenience and acceptability. Furthermore, an intervention like the one being studied could have spillover effects on the microbiology of the intensive care unit that could hamper the identification of the effects of the intervention.

Additionally, given restrictions on the study’s budget provided by the Brazilian Ministry of Health after December 31, 2023, we could not wait for all sites to be approved to initiate the study; therefore, the trial started once each center was approved. Coupled with an initial estimate of 50 centers, this staggered inclusion might lead to transitory imbalances in the recruitment rate of each group. However, we will address this in the analysis by considering the time period of each intervention. This time constraint on the trial also led to the choice of a one-month washout period. While more extended washout periods would be ideal to avoid cross-contamination of ICU-level microbiological effects of the intervention, the trial would be unable to be conducted within the planned time frame.

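### The primary model contains an allocation-by-period interaction and names no primary contrast, so as written it does not secure the within-ICU comparison

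*Protocol article*

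**What the plan says.** The protocol article (Statistical analysis) analyses the primary outcome, device-associated infections per 1,000 patient-days, with a Poisson generalised linear mixed model "with allocation group, study period, and the interaction of allocation group and study period as fixed effects and center as a random effect". The interaction is a term of the primary model itself, not a separate or preliminary test. The section does not name the coefficient or contrast that is the primary effect, the factor coding, or any averaging over periods.

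Three other statements bear on this:

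- The model is reused: "We will use the same model to evaluate the incidence per 1000 patient-days of each specific HCAI". The same sentence extends it to cultures positive for multidrug-resistant pathogens and to antibiotic use. (Mortality has its own specification and is not part of this point.)
- The model is left open in one respect: "Other possible distributions and models might be considered according to the variable’s behavior". That sentence concerns distribution and model choice and does not settle the contrast.
- On software: "All the statistical analyses will be performed using R software".

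The Design section describes each ICU delivering both kinds of bath "with crossover for a period of 3 to 6 months, depending on the time of each center’s entrance to the study", with a one-month washout. The Discussion gives the only reason for period terms, namely staggered entry of centres: "we will address this in the analysis by considering the time period of each intervention".

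**The concern.** With an interaction in the model, no single coefficient is automatically the overall treatment effect. Under reference coding, which R uses unless told otherwise, the allocation coefficient is the effect in whichever period is the reference level. In a crossover with two sequences and two periods, that single-period effect is a comparison between two different sets of ICUs, and the interaction is the same contrast as the difference between sequences.

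Two quite different rate ratios can therefore be read from one fitted model: a within-ICU effect averaged over periods, and a between-ICU effect from one period. They answer different questions with different precision, and the text does not choose between them. In an open-label trial, with the choice of model partly open, the contrast behind the headline p-value should not be left until results are visible. Because the model is reused, the same ambiguity reaches each specific infection, resistant cultures and antibiotic use.

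Staggered entry does not explain the interaction. A period main effect deals with a secular trend or a temporary imbalance in recruitment between groups.

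**Working it through.** **Inputs from the Sample size section.** The plan counts on 21 ICUs averaging 600 patients, which makes 12,600 in all. Event rate and heterogeneity are given as "a baseline rate of 6 HCAIs per 1,000 patient-days and a between-cluster variance of 0.6". The scale of the 0.6 is not stated, so two readings are carried:

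- variance of the log rate: s² = 0.6;
- variance of the rate per 1,000 patient-days: s² = 0.6/6² = 0.0167 on the log scale.

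**Assumptions, not in the article.** Two periods; the 600 patients split 300/300; equal numbers of ICUs per sequence (10.5 each, for the formula); 7 patient-days per patient, with 5 and 10 as the range; no extra ICU-by-period variation.

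**The plan's own figure.** The article gives no standard error. It states 80% power for a relative risk of 0.91. At 7 days per patient, neither contrast reproduces this: the chance of a significant result is about 18% with a standard error of 0.089 (the value when infections in the chlorhexidine arm are reduced by 9%) and about 4.5% with 0.361. That is a separate matter, depends on the assumed stay, and does not decide the present point.

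**Step 1. What each contrast compares.** Let A be the ICUs starting on chlorhexidine and B those starting on soap and water. A1, A2, B1 and B2 are their mean log rates in periods 1 and 2.

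- Reference-period coefficient: A1 − B1. Different ICUs.
- Interaction: (B2 − A2) − (A1 − B1) = (B1 + B2) − (A1 + A2). This is the sequence difference.
- Period average: ½[(A1 − B1) + (B2 − A2)] = ½[(A1 − A2) − (B1 − B2)]. Within-ICU differences only; the ICU effect cancels.

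**Step 2. Infections per ICU-period.** e = 300 × 7 × 0.006 = 12.6, so 1/e = 0.0794.

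**Step 3. Variances.**

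- Reference period: (s² + 1/e) × 4/21.
- Period average: ¼ × (2/e) × 4/21 = 2/(21e).
- Model without interaction: also 2/(21e).

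**Step 4. Results at 7 days.**

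| Reading of 0.6 | SE, reference-period coefficient | SE, period average | SE, no interaction | Variance ratio |
|---|---|---|---|---|
| Log scale, s² = 0.6 | √(0.6794 × 4/21) = 0.360 | √(2/264.6) = 0.087 | 0.087 | 17.1 |
| Rate scale, s² = 0.0167 | √(0.0960 × 4/21) = 0.135 | 0.087 | 0.087 | 2.4 |

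A generalised least squares calculation with a random ICU intercept gives the same values.

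**Step 5. Sensitivity.**

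- Stay of 5 or 10 days (e = 9 or 18): 0.368 versus 0.103 or 0.353 versus 0.073 for s² = 0.6; 0.156 versus 0.103 or 0.117 versus 0.073 for s² = 0.0167. The variance ratio runs from 12.8 to 23.6 and from 2.3 to 2.6.
- Intermediate log-scale variance of 0.1 at 7 days: 0.185 versus 0.087.
- Adding an ICU-by-period variance of 0.05 at s² = 0.6 and 7 days narrows the gap: 0.374 versus 0.113, a variance ratio of 11.0.
- Four periods with the same total number of patients and s² = 0.6: 0.380 versus 0.087 with two alternating sequences, and 0.209 versus 0.087 with four sequences. With s² = 0.0167, 0.183 and 0.181 versus 0.087.

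**Step 6. Simulation.** In 400 simulated trials at 7 days, fitted with a Poisson random-intercept model, the standard deviations were 0.336 for the reference-period coefficient, 0.077 for the period average and 0.076 without the interaction. The last two estimates correlated above 0.999.

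**The case against.** A reader might infer that including the interaction throws the within-ICU comparison away. The article does not support that. Steps 1 and 4 show that averaging the period-specific effects recovers the comparison at no cost in precision. The loss arises only if the reference-period coefficient is reported as the overall effect. The article does not say it will be, and naming R does not fix the coding.

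It can also be said that contrast coding belongs in a statistical analysis plan or supplement, neither of which is shown, and that a condensed article may leave it out. Silence on coding alone would indeed be no finding. Here, however, the article does state the model's terms, includes an interaction without giving a reason for it, and so creates an ambiguity that a model with main effects only would not have.

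Two further limits stand. Exact equivalence of interaction and sequence holds for two periods. Figure 1 is not shown, the study period is not defined, and the Discussion's wording is compatible with calendar time. With more levels the coefficient would still describe one level, but the figures would differ, as Step 5 shows. The size also depends heavily on the scale of the 0.6. A single statement of lost power would be unsupported, because it needs a length of stay that the article does not give.

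**Conclusion.** The point holds in this form: the primary model as written does not secure the within-ICU comparison for which the crossover was chosen, because it contains the interaction and names no primary contrast. If the allocation coefficient is taken under reference coding, the standard error of the log rate ratio rises from about 0.09 to about 0.36 with 0.6 as a log-scale variance, or to about 0.14 with 0.6 on the rate scale. These figures assume two periods, 21 ICUs, 300 patients per ICU-period and 7-day stays. The direction is the same under every reading tried; the size is not. The article does not show that the wrong contrast will be reported, only that nothing in it prevents this.

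**What to change.** Before the database closes, state the primary effect as one allocation rate ratio with its 95% CI, obtained in one of two equally precise ways:

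1. from a model with allocation and period as fixed main effects, the planned random effect for centre, and no interaction; or
2. from the present model, as the pre-specified average of the period-specific effects, with the averaging weights given.

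Define the levels of study period in the same place. Report allocation-by-period as a supplementary check only, and state that its result does not decide the primary analysis. Apply the same rule to the secondary outcomes that reuse the model.

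The cost is a sentence or two of analysis text. No data, sample size or trial conduct changes. If the database has already closed, the report should say when the contrast was fixed and whether that was before results by group were seen.
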